### Laboratory tests

The fasting serum samples will be transferred to the Department of Anthropology, University of Delhi, on dry ice for the generation of data on biochemical assays on all the mothers during each trimester and also on their offspring using cord blood. The available auto-analyzer (XL-640, ERBA Mannheim, Czech Republic) in the Department of Anthropology, University of Delhi, India, will be used for biochemistry data generation (ie, glucose, insulin, lipids, KFT and LFT) after ensuring daily calibration. Insulin levels will be estimated using ELISA kits. Furthermore, a reagent lot calibration will also be performed whenever there is a change in lot number of the reagents to estimate the variation in assays between two reagent lots. For internal quality control, one blank per 100 samples and one control sample from *UK National External Quality Assessment Service* of known concentrations will be run in every 200 samples. Moreover, one duplicate and one sample of known concentration from the previous batch will be run per 100 samples for assessing intra-assay and inter-assay variation, respectively, to help with analyses in confirming repeatability and reproducibility of biochemistry data. Finally, 5% of the samples will be run in a different laboratory for all the biochemical assays as a measure of external quality control. Moreover, information on participant’s blood group, Sickle hemoglobin (HbS)and HIV infection, which are the part of standard protocol of the hospital’s antenatal care, will be taken from PBM Hospital.

### Quantitative metabolomics

The quantitative data on the level of metabolites (in mothers during each trimester and in offspring using cord blood) will be generated through a targeted approach for screening the predefined and known metabolites using a commercial assay, that is, AbsoluteIDQ p400 HR kit (Biocrates Life Sciences, Innsbruck, Austria). It provides data on 400 endogenous metabolites from 11 metabolite classes (ie, amino acids, biogenic amines, monosaccharides, acylcarnitines, diglycerides, triglycerides, lysophosphatidylcholines, phosphatidylcholines, sphingomyelins, ceramides and cholesteryl esters). The choice of AbsoluteIDQ p400 HR kit based on proven utility of its previous version of kit (AbsoluteIDQ p180) in several metabolomics-based epidemiological studies.^9 95–98^ Our collaborator, the Phenome Centre Birmingham, University of Birmingham, UK, has experience of using this kit in an interlaboratory trial. For generating data on targeted metabolites, a triple quadrupole mass spectrometry-based technology will be used which characterises a metabolite by its molecular mass, its specific fractionation pattern (tandem mass spectrometry) and high sensitivity.^99^ The complete analytical process will be performed using the MetIQ software package, which is an integral part of these kits. The quality control procedure used by Suhre *et al*
100 will be followed for generation and cleaning of metabolomic data. One reference sample will be measured three times on each plate across the samples. The quality of metabolite data will be controlled by estimating their coefficient of variation and missing value rates.^15^ Outlying samples and data points will be excluded and finally all missing values will be imputed.^101^

### Body composition

The body composition of infants will be measured using a DXA machine (Osteo Pro Max, BM Technology, Korea) available in PBM Hospital, Bikaner. The machine will be calibrated using infant phantoms at regular intervals. We have developed a standard operating procedure with the help of published literature^102–104^ for neonatal scans of femur, spine and whole body. Newborns will be measured within 48 hours of delivery after feeding in a calm or sleeping state. Infants will be swaddled in a thin cotton blanket in the required position and measurement will be taken without any metals, buttons or pins on the infant. The region of interest (ROI) for anterior-posterior spine will be five vertebral bodies of the lumber region; for femur scan this will include the femoral neck, trochanters, intertrochanteric and total hip regions. For the whole body scan, the infant will be positioned at the centre of the table, aligned in a straight line from the nose, centre of the body and down through the knees and toes. Six ROIs will be taken for the whole body scan (head, entire right and left arms, right and left leg regions and trunk).

### Data capture, protection and management

The data are being recorded in paper-based questionnaires that will be initially entered in Microsoft Excel, and later transferred to a SQL-based database to be developed in collaboration with the University of Bristol, UK. The master data will be stored at multiple locations (at least two) and managed in computers available in the Department of Anthropology, University of Delhi. One unique identification number (UID) is being assigned to each study participant (mothers) that will be common for her questionnaire-based information, biological measurements, blood and other biological samples. Similarly, newborns will also be assigned a UID which is linked to the UID of mothers. The computers will be password protected, and UID linked with personal identifiers necessary for contact and future follow up, will be encrypted and held separately in a different system and backed up regularly. All the biological samples will be collected in pre-assigned bar-coded tubes and vials and will be stored at −80°C in Bikaner, Rajasthan. A comprehensive data dictionary will be prepared for all the study variables and the entire data will be regularly checked for outliers, distribution of variables and missingness.

### Data analyses

The evaluation of cross-sectional associations of maternal body weight with quantitative metabolite levels in each trimester, independently, will be done using regression-based modelling. Both level of metabolites and gestational weight in each trimester will act as exposure as well as outcome. Variables like socioeconomic position, gestational age, parity, diet, smoking and physical activity will be considered as confounders. Maternal characteristics will be considered as exposures (like trimester-specific weight, metabolite levels) to evaluate their association with offspring-related outcomes (fetal growth, birth weight, body compositions and metabolite levels). The potential confounders for maternal-offspring associations will be socioeconomic position, gestational age, parity, diet, sex of the offspring, smoking and physical activity.

Mixed effects regression models for repeated measures will be applied for examining longitudinal associations of weight gain from first to third trimester^42^ with maternal levels of metabolites during pregnancy and fetal growth.^105^ We will also analyse the associations of level of metabolites from first to third trimester with trajectories of GWG. Mediation analyses will be conducted for evaluating the role of maternal metabolites as intermediates between GWG and offspring’s body composition.^106^ False discovery rate based multiple testing correction for number of metabolites will be applied.^107^ Mediation analysis will be conducted to examine whether the effect of GWG on fetal growth is mediated through alteration in levels of circulating metabolites.

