### Relationships between maternal gestational weight gain and newborn health

Gestational weight gain (GWG) is a complex biological trait which is influenced by maternal physiology, maternal, placental and fetal metabolism.^28^ There are short-term or long-term implications of inadequate or excessive GWG which direct the trade-off between maternal and child health outcomes.^28–32^ For example, inadequate weight gain is associated with high risks of low birth weight, small for gestational age and preterm birth.^33^ Excessive GWG is associated with large for gestational age, gestational diabetes, caesarean section and postpartum weight retention.^34^ Furthermore, high prepregnancy maternal body mass index (BMI) is associated with perturbations to maternal metabolome across gestation.^35^

Maternal GWG is a good indicator of fetal nutrition.^36^ Any amount of weight gain in the first 14 weeks and high rate of weight gain (>500 g/week) in 14–36 weeks are associated with raised adiposity in the offspring.^37^ GWG in the first trimester is associated with offspring BMI from infancy to early childhood whereas excessive GWG (ie, ≥500 g/week) in second and third trimesters is associated with increased birth weight.^38^ In the first half of the pregnancy (<20 weeks), excessive GWG is associated with higher birth weight and high body fat in newborns compared with the second half of pregnancy.^39^ Furthermore, Gaillard *et al*

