## Assessment procedures and instrumentation

### Ultrasound measures

For ultrasound-based measurements relating to fetal growth, we are using the existing standard operating procedures described by INTERGROWTH study^76^ to ensure reliable data collection. The data are being collected by trained sonographers in Bikaner, who are highly familiar with the equipment (SonoACE R7 Samsung Healthcare) and experienced in conducting ultrasound examinations. The intraobserver variation will be assessed by repeat sonographic measurements on 10 participants on the same day. Comparisons will also be made between the readings of two sonographers of the hospital on 10 participants to assess interobserver variability. The interequipment variation in ultrasound measures will be assessed by comparing the PBM results of 10 participants with the radiology laboratory outside the hospital. We will measure the crown-rump length (CRL), biparietal diameter, occipitofrontal diameter, head circumference, femur length, anterior-posterior abdominal diameter. Gestational age based on CRL and fetal weight will be estimated with the help of INTERGROWTH equations.^76 77^

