### Questionnaires

A comprehensive questionnaire has been developed for collecting information on demographic, anthropological (caste, religion and consanguinity), medical disease history, tobacco and alcohol intake and passive smoking. The validated food frequency questionnaire of '*Indian Migration Study'* is being used for evaluating dietary intake.^79^ Maternal physical activity during pregnancy is being assessed using the international physical activity questionnaire (ie, 7 days long).^80–82^ The assets-based tool of National Family Health Survey-4 is being used to evaluate socioeconomic position.^83^ For assessing depression, we are using the Patient Health Questionnaire^84^ and Edinburgh Postnatal Depression scale.^85^ The WHO-5 questionnaire is being used for collecting information on quality of life.^86^ The capability well-being, that is, individual’s freedom to function in five key areas of their life: ’stability', ’attachment', ’achievement', ’autonomy' and ’enjoyment', is being assessed by using the ICEpop CAPability measure for Adults.^87–89^ Information on maternal environment, gynaecological and obstetrics history is also being collected using tools adapted from INTERGROWTH study.^90 91^ Additionally, a structured questionnaire on social factors like relationships with family members, husband position in household, social support during pregnancy and travel is being used for assessing the quality of social life and adequacy of social support (table 1).

**Table 1 T1:** Measures, tools and time points of data collection

	Mother			Offspring
	First trimester	Second trimester	Third trimester	
Timing of data collection	10th to 13th weeks	22nd to 24th weeks	32nd to 34th weeks	Birth
Gynaecological and obstetric	✔	✔	✔	–
Socioeconomic position	✔	✔	✔	–
Anthropological (caste and religion)	✔	✔	✔	–
Education	✔	✔	✔	–
Marital status	✔	✔	✔	–
Smoking	✔	✔	✔	–
Alcohol drinking	✔	✔	✔	–
Medication	✔	✔	✔	–
Disease history	✔	✔	✔	–
Maternal environment	✔	✔	✔	–
Physical activity (IPAQ)	✔	✔	✔	–
Time-activity pattern	✔	✔	✔	–
Food frequency	✔	✔	✔	–
Dietary recall (3 days)	✔	✔	✔	–
PHQ-12	✔	✔	✔	–
Well-being (WHO-5)	✔	✔	✔	–
Depression (EPNDS)	✔	✔	✔	–
Social factors	✔	✔	✔	–
Capability well-being (ICECAP-A)	✔	✔	✔	–
Anthropometry				
Height/body length	✔	✔	✔	✔
Sitting height	✔	✔	✔	–
Weight	✔	✔	✔	✔
Circumferences	✔	✔	✔	✔
Skinfolds	✔	✔	✔	✔
Blood pressure	✔	✔	✔	–
Laboratory tests: Glucose, insulin, Hb, lipids, LFT and KFT and blood group	✔	✔	✔	✔
Metabolomic data	✔	✔	✔	✔

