### Adult anthropometry

The assessment of anthropometric traits (weight, height, sitting height, circumferences and skinfolds) are being performed on study participants using standard procedures.^92^

Weight is being measured when the participant standing straight on the centre of the weighing machine (Tanita, model-HD380), arms hanging freely with minimum clothes and without accessories. Height is being measured as the vertical distance between vertex (highest point on head) and floor when the participant standing straight with feet together on the level floor without footwear, arms resting by the side, with head in eye-ear plane (Frankfort horizontal plane) and heels, buttocks and shoulders projected on the vertical plane using a wall-mounted stadiometer (ADE, Germany, model-MZ10023-3). Sitting height is being measured as the maximum distance from the vertex (top of the head) to the base of a flat sitting surface, with legs hanging freely and head in eye-ear plane.

Circumferences are being measured at the specific landmarks when the plane of the tape (ADE, model-MZ10021) is perpendicular to the long axis of the body and parallel to the floor without tape being pulled too loose or too tight. Waist circumference is being measured at the narrowest point (which is an approximate midpoint) around the waist between the lower rib margin of the last palpable rib and the top of the iliac crest with the help of a measuring tape. Mid-upper arm circumference is being measured at the midpoint between the tip of the shoulder and the tip of the elbow (acromion and olecranon process, respectively) taken horizontally (at the middle of the biceps). Hip circumference is being measured at the widest part of the hip (buttock) at the level of the trochanterion, which is the most superior point on the greater trochanter of the femur, not the most lateral point. Calf circumference is being measured on the right leg as the maximum circumference in a plane perpendicular to the long axis of the calf until the greatest circumference is located when foot is placed on raised platform.

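### Weight gain measured to 32–34 weeks contains the fetus, so its association with fetal growth, and the mediation analysis built on it, is partly mechanical

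*Protocol article*

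**What the plan says.** Exposure. The Data analyses section plans repeated-measures models over the whole of follow-up: "Mixed effects regression models for repeated measures will be applied for examining longitudinal associations of weight gain from first to third trimester", related to maternal metabolites and to fetal growth. It also says "Maternal characteristics will be considered as exposures (like trimester-specific weight, metabolite levels) to evaluate their association with offspring-related outcomes (fetal growth, birth weight", and goes on to list body composition and metabolite levels.

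Mediation. Two analyses are named. One is "Mediation analysis will be conducted to examine whether the effect of GWG on fetal growth is mediated through alteration in levels of circulating metabolites". The other is "Mediation analyses will be conducted for evaluating the role of maternal metabolites as intermediates between GWG and offspring’s body composition".

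Measurement. Under Adult anthropometry, "Weight is being measured when the participant standing straight on the centre of the weighing machine", so weight is the scale weight of the pregnant woman. Table 1 puts the last maternal weight at the "32nd to 34th weeks" visit, together with the third ultrasound.

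Fetal weight. Under Ultrasound measures, "Gestational age based on CRL and fetal weight will be estimated with the help of INTERGROWTH equations". No use of that estimate to correct maternal gain is stated. The confounders listed for maternal-offspring models contain no term for fetal or conceptus weight.

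The background recognises the issue in general terms, "Gestational weight gain (GWG) is a complex biological trait which is influenced by maternal physiology, maternal, placental and fetal metabolism", but the analysis section does not carry it through.

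**The concern.** At 32–34 weeks the fetus is on the scale with the mother. A woman carrying a larger fetus has, other things equal, a larger recorded gain and a larger fetal weight at the same visit. The plan regresses the part (fetal size) on a whole that contains it (GWG) and calls the result an effect of GWG. Some positive association is then guaranteed even if maternal tissue gain does nothing to the fetus.

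The mediation analyses are the more exposed. They split a total effect into a direct part and a part through metabolites, and the article presents the pathway between GWG and offspring health as the open question. A total effect that includes the weight of the fetus does not split into quantities with the intended meaning.

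**Working it through.** The article states no figure for GWG against fetal growth or for mediation. Its power figures concern other contrasts (weight to metabolite, metabolite to fetal growth). So there is no figure to reproduce, and the SDs below are assumptions.

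**1. Built-in association under no true effect.** Write gain to 32–34 weeks as G = M + F, where M is non-fetal gain (SD s_M) and F is fetal weight at that visit (SD s_F), independent of M. Then r = s_F/√(s_M² + s_F²), and the slope of F on G is s_F²/(s_M² + s_F²). Detection is from Fisher z with n = 1000 and two-sided α = 0.05.

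| s_M (kg) | s_F (kg) | r | R² | slope (g per kg) | p < 0.05 |
|---|---|---|---|---|---|
| 2 | 0.2 | 0.100 | 0.99% | 10 | 88% |
| 2 | 0.3 | 0.148 | 2.20% | 22 | 99.7% |
| 3 | 0.2 | 0.067 | 0.44% | 4 | 56% |
| 3 | 0.3 | 0.100 | 0.99% | 10 | 88% |
| 5 | 0.2 | 0.040 | 0.16% | 2 | 24% |
| 5 | 0.3 | 0.060 | 0.36% | 4 | 47% |

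These figures are before covariate adjustment.

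**2. Gain to 22–24 weeks.** Assume fetal SD 0.07–0.08 kg and gain SD 1.5–2 kg. Then r = 0.07/√(2² + 0.07²) = 0.035 to 0.08/√(1.5² + 0.08²) = 0.053.

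**3. Birth outcomes.** Birth weight is not inside a weight taken at 32–34 weeks. Under the same model its built-in correlation with G is r multiplied by the correlation between F and birth weight, so it is smaller than the r in step 1. The same holds for body composition.

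**4. Mediation.** Linear models, 1,000,000 simulated women, s_M = 3.5 kg. The metabolite is standardised, with correlation 0.3 to whatever drives it. In the second row it adds 0.1 kg of fetal weight per SD, and the fetal SD is the part it does not explain. Entries are total / direct / indirect in g per kg of gain, with the proportion mediated where meaningful.

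| Truth | gross gain, fetal SD 0.25 kg | gross gain, fetal SD 0.5 kg (beyond the range in step 1) | net gain |
|---|---|---|---|
| No effect; metabolite follows maternal gain | 5.1 / 5.6 / −0.5 | 20.0 / 22.0 / −2.0 | all about 0 |
| Complete mediation | 14.2 / 5.7 / 8.5 (60%) | 28.8 / 22.0 / 6.8 (24%) | 8.6 / about 0 / 8.5–8.6 (99%–100%) |
| No effect; metabolite follows fetal size | 5.1 / 4.6 / 0.5 (9%) | 20.0 / 18.2 / 1.8 (9%) | all about 0 |

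Hand check of the first total: 0.25²/(3.5² + 0.25²) = 0.0625/12.3125 = 0.0051 kg per kg.

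Gross gain inflates the total and direct effects in every row. It understates mediation when mediation is complete, and it produces a false indirect effect when the fetus drives the metabolite.

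**5. What subtraction leaves behind.** Take as an upper case a conceptus SD of 0.45 kg, fully proportional to fetal weight, with fetal SD 0.25–0.30 kg. Subtracting the fetus leaves an SD of 0.15–0.20 kg. The residual R² is 0.15²/(3.5² + 0.15²) = 0.2% to 0.20²/(2.5² + 0.20²) = 0.6%.

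**The case against.** The strongest reply is that the overlap is narrow, and much of that is right.

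- A reader might infer that every offspring outcome is contained in GWG gram for gram. The documents do not support this. Only fetal weight at the third-trimester visit overlaps literally. Birth weight and DXA measures come later and are linked through fetal size alone.
- A reader might set the built-in R² against the 2% of fetal-growth variation in the Sample size section. That 2% is for a maternal metabolite as predictor at α = 0.0001, a different contrast and threshold, so the comparison should not be made.
- A reader might extend the point to metabolite regressions on third-trimester weight. There the fetus is not the outcome, and the exposure is total body weight, in which fetal variation is a small share. The point does not reach those models, nor the analyses with metabolites as the exposure.
- A reader might say that the mechanical part can never pass through a metabolite. The third row of the mediation table shows otherwise.

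It can also be said that the mediation sentences give no window for GWG, that the article elsewhere frames first-trimester gain as the exposure for later metabolites, and that deriving the variable belongs to the fuller plan. This stands in part: if the window were early, little would remain. But the mixed models explicitly run from first to third trimester with fetal growth as an outcome, and nothing restricts the mediation analyses to early gain.

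Finally, GWG is a recognised composite trait, gross gain is a legitimate quantity, and the effect of GWG on fetal growth is not itself a listed objective. That argues for keeping gross gain in the report and against calling the flaw fatal. It does not justify reading gross gain as a cause of the fetal weight it contains.

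**Conclusion.** The point holds for gain measured to 32–34 weeks: directly for fetal weight at that visit, and indirectly for birth weight and newborn body composition. With no true effect of maternal tissue gain, the built-in correlation with concurrent fetal weight is about 0.04–0.15 (R² 0.2%–2.2%). This rests on assumed SDs, independence of fetal and non-fetal gain, and no covariate adjustment. It is small, yet at n = 1000 it would reach p < 0.05 in 24% to nearly all studies across that range. Gain to 22–24 weeks is little affected.

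The mediation analyses matter most, because even a modest mechanical part can be large relative to a small true effect. In the simulated case of complete mediation with a true effect of 8.6 g per kg and fetal SD 0.25 kg, the proportion mediated came out at 60%. This should be changed, but it does not undermine the study as a whole.

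**What to change.** 1. Where gain to 32–34 weeks is the exposure for birth weight, newborn body composition or their mediation models, analyse net gain: maternal weight at that visit, minus ultrasound-estimated fetal weight at that visit, minus first-visit weight. Report gross gain alongside it.
2. For in-utero growth and its mediation, use gain to 22–24 weeks as the exposure for growth from 22–24 to 32–34 weeks. This also puts exposure before outcome. Gross gain is adequate here: subtracting the 22–24 week estimate would put that scan's error on both sides.
3. State that any mediated proportion from gross gain to 32–34 weeks includes the weight of the fetus.

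Cost: one derived variable and a few sentences, with no new data. Ultrasound error enters net gain. If the 32–34 week scan were used on both sides, an assumed error SD of 0.16–0.20 kg, with fetal SD 0.25 kg and non-fetal SD 3 kg, would create r = −0.16²/(√(3² + 0.16²) × √(0.25² + 0.16²)) = −0.03 to −0.20²/(√(3² + 0.20²) × √(0.25² + 0.20²)) = −0.04. Item 2 avoids this. Placenta and amniotic fluid remain in net gain, so the correction is partial and the report should say so.
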